### Secondary outcome measures

Additionally, the character of pain, number of pain locations and distribution of symptoms will be evaluated with a body diagram. Neck specific disability will be measured by the Neck Disability Index [36, 37]. Headache and dizziness will be measured on the VAS and Dizziness Handicap Inventory (DHI) [38]. Symptom satisfaction related to the neck problems will be rated on a seven-grade scale [39]. Self-efficacy will be measured on the Self-efficacy scale [40] and Exercise Self-efficacy scale. Fear-avoidance beliefs will be measured with the Fear Avoidance Beliefs questionnaire (FABQ) [41, 42] and Tampa Scale of Kinesiophobia (TSK) [42]. Hostility, anxiety and depression will be measured with the HAD scale [43, 44]. Coping strategies will be measured with the Coping Strategy Questionnaire (CSQ) [45]. Pain catastrophizing will be measured with the Pain Catastrophizing Scale (PCS) [46]. Health related quality of life assessed by the EuroQuol five dimensions self-classifier (EQ-5D) and current health state by the EuroQuol vertical VAS (0–100 mm) [47]. Physical activity will be measured with International Physical Activity Questionnaire (IPAQ short version) [48] and a scale for assessment of physical activity [49]. Patient specific goals will be measured with the Patient specific functional scale (PSFS) [50] and the Patient Goal Priority Questionnaire (PGPQ) [51]. Work ability will be measured by the Work Ability Index (WAI) [52].

*Additional questions* of fulfillment and satisfaction which will be asked after the intervention at the 6 and 24 months follow-ups such as: -adherence to the intervention, -treatment expectations fulfilled, - if they would recommend the intervention to patients with similar problems and if surgery or other interventions have been undertaken.

### Confidentiality

To guarantee the patients’ confidentiality all data collected will be coded and the codes will be locked in and stored separate from collected data.

### Intervention groups

Each physiotherapist who will treat patients in the study has been trained in the intervention program by the test leader who is a specialised physiotherapist at the specialist clinic. The entire treatment approach is documented in a manual of standard operating procedures and given to the treating physiotherapist. All exercise performed and progression of each will be registered in a diary. The written information is also available for the patients. For both groups the intervention period is 14 weeks.

#### Neck specific training

Active physical rehabilitation including neck-specific training with an additional cognitive behavioural approach will be included. The goal of the intervention is to improve physical functioning with specific respect to sensorimotor function, neck muscle strength and endurance as well as reducing pain. The active physiotherapy rehabilitation program consists of a standardised program (three times a week) with medical exercise therapy and if needed vestibular rehabilitation. At the start of the intervention motivational interviewing will be included. Additionally once a week during the first 14 weeks of the program (Week 1–14) the physiotherapist will educate the patient about physiology of pain, stress, exercise, breathing, relaxation, coping, pacing and ergonomics. The physiotherapist will also teach and have a discussion with the patient on how to manage the pain at home both physically with; heat, cold or TENS and psychologically with; relaxation training, exercises for increased body awareness as well as goal setting for better coping strategies and self-efficacy. Throughout the treatment program a cognitive approach from the physiotherapist according to theoretical behaviour change models will be used. Home exercises will also be prescribed. All physiotherapists will be provided with a well-defined frame of exercises with a standardised and structured progression. After a clinical examination the physiotherapist adjusts the program for each patient according to the selection of exercise and dosages chosen. From week 15–20 the patients have the opportunity to meet the physiotherapist for discussion, encouragement and help with exercise progression and otherwise do exercise on their own in the clinic or at home.

#### Prescribed physical activity

Physical activity will be formally prescribed by a physiotherapist and followed up according to customary routines [53, 54]. Prescribed physical activity is a tailored physical activity programme with the monitoring of progress and a follow-up. In guidelines for prescribing physical activity a cognitive behavioural approach (theoretical behaviour change model) with motivational interviewing is included. The interview includes exploratory talk, commitment/decision, life style change, health promotion, evaluation of readiness for change, reflection, assessment of motivation, patient specific goal assessment, conclusion and plan for follow-up at 14 weeks. Patients are guided by the physiotherapist to increase their overall activity and general strength with i.e. walking and other self-mediated activities and exercise. During the intervention and follow up period to 20 weeks the patients are free to contact their physiotherapist and the number of contacts will be registered.

The interventions will be led by experienced and specialised physiotherapists. The patients in the neck specific training group will have personal contacts with their physiotherapist whereas in the prescribed physical activity group they do not have scheduled regular contacts but the opportunity to contact the physiotherapist when needed. An earlier study of patients after lumbar disc surgery showed good results for an intervention based on home training when patients have received careful instructions and have access to the physiotherapist if questions arise [55].

### Data analysis

Outcome data from the two groups will be compared using an intention to treat analysis with all patients being analysed in the group to which they were originally randomly assigned even though they are lost to follow-up or non-compliance of the intervention or any other deviation from the protocol [56]. In the intention to treat analysis the technique multiple imputation of missing data will be used [57]. Continuous or discrete data will be compared with parametric or non-parametric statistical methods depending on possible skewness in the data distribution. Categorical data will be compared with non-parametric statistics. For relationships among several independent variables against a dependent variable multiple regression analysis will be used. Cost-effectiveness of the treatment models due to direct and indirect costs will be calculated.

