### Sample size

The sample size is based on data from the “Swedish neck study” [12, 13]. A sample size of 56 in each group will have 80% power to detect differences in means of 15 mm assuming that the common standard deviation is 28 mm using two group t-test with a 0.05 two-sided significance level. A drop-out rate of 20% was calculated for.

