### Randomisation

After the baseline assessment, each patient will be randomised to one of two interventions: A) active physical rehabilitation with a neck specific exercise program including a cognitive behavioral approach (neck-specific training) or B) prescribed, self-mediated and progressive physical activity (prescribed physical activity). See flow chart (Figure 1). Randomisation will be done in blocks of eight according to a computer generated randomisation list prepared by an independent statistician not involved with subject recruitment. The sequence of allocation to either intervention will be concealed and performed by a person not involved in the testing or treatment of subjects in the project according to the random generated computer list and kept in numbered and sealed envelopes.

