### Primary outcome measure

The primary outcome measure is pain intensity. Intensity of neck pain and arm pain is measured on a Visual Analogue Scale (VAS) (0–100 mm) [34, 35]. Pain will be measured before intervention, 3, 6, 12 and 24 months after the start of the intervention.

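### No baseline covariate is named for the primary pain comparison, although VAS is measured on every patient before randomisation: precision is given up that would cost nothing to keep

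*Protocol article*

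**What the plan says.** The primary outcome is pain: "Intensity of neck pain and arm pain is measured on a Visual Analogue Scale (VAS) (0–100 mm"). On timing, the same section (Primary outcome measure) adds: "Pain will be measured before intervention, 3, 6, 12 and 24 months after the start of the intervention". The baseline score comes before allocation: "After the baseline assessment, each patient will be randomised to one of two interventions" (Randomisation). That section describes blocks of eight and names no stratification factor.

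The trial is sized without reference to baseline: "A sample size of 56 in each group will have 80% power to detect differences in means of 15 mm" (Sample size). The SD behind this figure is 28 mm in both arms, and the calculation is for a two-sided t-test at the 5% level.

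On analysis, "Outcome data from the two groups will be compared using an intention to treat analysis" (Data analysis). Missing values are to be multiply imputed. Continuous outcomes are to be compared parametrically or non-parametrically, according to how skewed they are. Multiple regression is mentioned for relating several independent variables to a dependent one, without being tied to the treatment comparison. No covariate is named for that comparison.

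**The concern.** A choice between parametric and non-parametric methods made on skewness, next to a sample size built on a two-group t-test, reads most naturally as a t-test or its rank counterpart. On that reading the patient's own starting pain does not enter the comparison. Baseline VAS is a valid covariate because it is recorded before allocation, and nothing in the stated randomisation balances it.

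Two things are at stake. First, the part of the follow-up variance that baseline explains stays in the standard error, so the confidence interval is wider than it need be. Second, a chance difference in baseline pain between the arms passes partly into the observed follow-up difference. A rank test would also give no mean difference in mm to set against the 15 mm target.

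**Working it through.** **Inputs from the protocol article (Sample size, and the total of 144 under Participant selection):** difference 15 mm, common SD 28 mm, two-sided alpha 0.05, 56 per arm, 80% power, 20% drop-out, 144 in total.

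**Assumptions (not in the document):** 28 mm is the raw SD of VAS at follow-up; the baseline SD is also 28 mm (needed only for step 3); the baseline to follow-up correlation r lies between 0.3 and 0.7.

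**Step 1: reproduce the plan's figure.** The standard error of the difference is 28 × √(2/56) = 5.29 mm, and the noncentrality is 15/5.29 = 2.83. The noncentral t distribution gives 80.2% power at 56 per arm; solving for 80% gives 55.7, so 56. Allowing for drop-out, 56/(1 − 0.20) = 70 per arm, or 140 in total; 144 is the next multiple of the block size of eight. The stated figure is right.

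**Step 2: adjust for baseline.** With baseline as covariate the residual SD is 28 × √(1 − r²). The standard error is that SD × √(2/56), and the approximate half-width of the 95% CI is 1.96 times the standard error. The one degree of freedom spent on the covariate is ignored.

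| r (assumed) | Variance removed (r²) | Residual SD, mm | SE, mm | 95% CI half-width, mm | Power at 56 per arm |
|---|---|---|---|---|---|
| no adjustment | 0% | 28.0 | 5.29 | 10.4 | 80.2% |
| 0.3 | 9% | 26.7 | 5.05 | 9.9 | 83.8% |
| 0.5 | 25% | 24.2 | 4.58 | 9.0 | 90% |
| 0.7 | 49% | 20.0 | 3.78 | 7.4 | 97.6% |

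**Step 3: chance imbalance at baseline.** The standard error of the baseline difference is 28 × √(2/56) = 5.29 mm at 56 per arm and 28 × √(2/72) = 4.67 mm at 72 per arm. A gap above 5 mm in either direction then has probability of about 34% and 28% respectively. With equal SDs at baseline and follow-up, the share of a gap that carries into a comparison of final values is r. A 5 mm gap therefore moves it by 0.3 × 5 = 1.5 mm, 0.5 × 5 = 2.5 mm or 0.7 × 5 = 3.5 mm. Against the 15 mm target that is 10% to 23%.

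**Step 4: the choice of estimator matters.** A t-test on change scores has SD 28 × √(2(1 − r)). Its power at 56 per arm is 66% at r = 0.3, 80% at r = 0.5 and 95% at r = 0.7. Adjustment does better at each of these (84%, 90% and 98%).

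**The case against.** The strongest reply is that the article never says the comparison is unadjusted. ANCOVA and repeated-measures models are parametric methods, and the wording excludes neither. The t-test appears only in the sample size, and sizing on an unadjusted test while analysing with adjustment is common and conservative. Covariates are often left to a statistical analysis plan or full protocol, and neither is at hand. All of this stands, and it limits the point to a recommendation.

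A reader might infer several stronger claims that the documents do not support:

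- **The plan commits to an unadjusted test and keeps baseline pain out.** That is a natural reading, not a statement. The regression sentence does not rule out a model of follow-up VAS on arm and baseline, though it does not name one.
- **Each follow-up visit is tested separately.** The article lists measurement times and does not say how the visits are modelled.
- **The trial is underpowered.** On its own inputs it is not (step 1).
- **Chance imbalance biases the result.** Under concealed randomisation it does not, and the unadjusted test keeps its type I error. Imbalance affects precision and the estimate given the baseline actually observed. Most trials of this size would have a gap below 5 mm, and only a fraction of any gap carries over.

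The size of the gain also rests on inputs from outside the document. The article does not say whether 28 mm is a baseline, follow-up or change-score SD; if it is not a raw follow-up SD, the table does not apply as it stands.

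What remains is that the method as described names no covariate, and a better one is available from data already being collected.

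**Conclusion.** The point holds as a free improvement, not as the correction of an error. On the assumptions listed, adjustment raises power at 56 per arm from about 80% to between 84% and 98%, with 90% at a correlation of 0.5, and narrows the 95% CI half-width from about 10.4 mm to between 9.9 and 7.4 mm. It also removes the 1.5 to 3.5 mm shift that a 5 mm baseline gap would cause. The direction of the gain depends only on baseline pain predicting follow-up pain; its size depends on a correlation that the article does not give.

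**What to change.** State in the Data analysis section that neck VAS and arm VAS at follow-up are each compared between arms by ANCOVA within each imputed data set, with the patient's own baseline value of that scale as covariate. A linear mixed model with arm, visit, arm-by-visit and baseline VAS is an equivalent choice for using all four follow-ups. Report the adjusted mean difference in mm with its 95% CI. Include arm and baseline VAS in the imputation model, so that imputation and analysis agree. The sample size can stay as it is. If an analysis plan already specifies this, a one-line reference to it in the protocol is enough.

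The cost is wording only: no extra measurements, visits or patients.

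### The skewness rule lets the outcome data choose between a mean and a rank comparison for the primary VAS scores, but only the mean comparison tests the 15 mm difference the trial is sized on

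*Protocol article*

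**What the plan says.** The Data analysis section gives one rule for every outcome that is not categorical: "Continuous or discrete data will be compared with parametric or non-parametric statistical methods depending on possible skewness in the data distribution". It does not say how skewness is judged, on which data, or which non-parametric test follows, and it does not exempt the primary outcome.

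The Primary outcome measure section makes pain intensity primary. Neck pain and arm pain are each scored on a 0–100 mm VAS at baseline and at 3, 6, 12 and 24 months.

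The Sample size section fixes the target: "A sample size of 56 in each group will have 80% power to detect differences in means of 15 mm". The calculation takes an SD of 28 mm in both arms and a t-test at the two-sided 5% level, and it makes an allowance of 20% for drop-out.

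The Data analysis section also plans for missing values: "In the intention to treat analysis the technique multiple imputation of missing data will be used".

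**The concern.** The rule makes the primary test depend on the outcome data. With two pain scores at four follow-up visits it can be applied 2 × 4 = 8 times, and nothing keeps the choice the same across them.

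The two branches also ask different questions. A t-test or a linear model addresses the difference in mean VAS in mm. A Mann–Whitney type test addresses whether a patient in one arm tends to score lower than a patient in the other, that is, whether P(X<Y) differs from one half. The two agree on what counts as no effect only under extra conditions, such as equal shape in both arms. Equal shape is doubtful on a bounded pain scale if one treatment produces clear responders and non-responders.

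At stake is whether the primary result answers the question the trial was sized for. Results at different visits could rest on different hypotheses. With no stated criterion, the choice of test is also open to challenge afterwards.

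There is a smaller practical difficulty with multiple imputation. Completed data sets may differ in whether they look skewed, and a rank-test p-value alone has no estimate and standard error to enter into Rubin's rules.

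**Working it through.** **1. The plan's own figure.** Inputs from the Sample size section: difference 15 mm, SD 28 mm, two-sided 0.05, two-group t-test, 56 per group.

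- Noncentrality = 15 / (28 × √(2/56)) = 2.835, with 2 × 56 − 2 = 110 degrees of freedom and a critical value of 1.982.
- Exact power is 80.2% at 56 per group and 79.5% at 55, so 56 is the smallest number that reaches 80%.
- Allowing for drop-out: 56 / 0.8 = 70 per group, 140 in total. The planned 144 is slightly above this and is a multiple of the block size of eight.

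The sample size reproduces, and it is a calculation for a difference in means.

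**2. What the rule does, by simulation.** The documents give no distributions and no skewness criterion, so everything in this step is assumed:

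- VAS scores follow a beta distribution on 0–100. For mean m and SD s as fractions of 100, k = m(1 − m)/s² − 1, and the parameters are mk and (1 − m)k. For example, mean 30 and SD 28 give k = 0.21/0.0784 − 1 = 1.679.
- Skewness is judged by a formal test at 0.05 on the residuals of both arms together. If it is significant, Mann–Whitney is used; otherwise Welch t.
- For the rows below other than SD 27 vs 19, there are 20,000 simulated trials with 58 per arm (144 × 0.8 / 2 = 57.6). The SD 27 vs 19 row is quoted to the nearest percent; with 56 or 58 per arm it comes to the same.

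Rejection rates:

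| Assumed arms (mean, SD) | Welch t | Rank test | Skewness rule |
|---|---|---|---|
| 30, 28 vs 30, 28 (identical) | 5.1% | 5.1% | 5.2% |
| 35, 27 vs 35, 19 (equal means) | about 5% | about 9% | about 10% |
| 30, 28 vs 30, 18 (equal means) | 5.3% | 19.6% | 20.5% |
| 25, 28 vs 40, 28 (15 mm, skewed) | 80.7% | 92.1% | 91.8% |
| 40, 28 vs 55, 28 (15 mm, little skew) | 81.4% | 81.1% | 81.4% |

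**3. Reading the table.**

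- In the third row the mean difference is zero, but P(X<Y) is 0.56 and the medians differ by about 6 mm. The rank test responds to that difference. Almost all the excess over 5% comes from the rank branch and very little from the preliminary skewness test.
- In the fourth row the difference in means is 15 mm and the difference in medians about 23 mm. The two tests reach opposite conclusions in 11.4% of simulated trials, so the choice of branch can decide the result.
- In the last row there is little skew and the choice hardly matters.

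**4. If the rank branch were the planned analysis.** With normal data its relative efficiency is 3/π, so 56 × π/3 = 58.6, or 59 per group. After drop-out this is 59 / 0.8 = 73.75, or 74 per group and 148 in total. The stated 144 therefore belongs to the mean-based branch.

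**The case against.** The strongest reply is that this is one generic sentence in a journal article. It covers many secondary scales, a good number of them ordinal, for which rank methods are reasonable, and an analysis plan that is not shown may fix the VAS method. That stands for the secondary scales. It does not remove the point for the primary outcome, because the article states a rule, and as written the rule covers the VAS.

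Four stronger readings are tempting, and the documents do not support them.

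- *The type I error is broken.* With identical distributions the rule rejects at about 5%. The inflation concerns the hypothesis of equal means when shapes differ, and a rank test that rejects there is detecting a real difference in distribution. Its size also depends on how skewness is judged. With scores from responder/non-responder mixtures (SD about 19 vs 27), one set of runs gave 5.5–6.5% when skewness was judged on pooled scores, 7.1–7.9% by group and 7.6–8.4% on residuals, while another gave 9.6%.
- *Rank tests cannot be combined with multiple imputation.* They can, for example through an estimate of P(X<Y), a Hodges–Lehmann shift with its standard error, or a normalised rank statistic. Only the bare p-value does not pool directly. Leaving the pooling method to an analysis plan is ordinary practice.
- *The primary effect size will be lost.* The rule governs how groups are compared. It does not say that mean differences and intervals will go unreported.
- *The sample size is wrong or power is lost.* The figure reproduces, and under skew the rule gains power for the rank hypothesis.

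These replies narrow the point. They do not answer the mismatch between the rank branch and the target in the Sample size section.

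**Conclusion.** The point holds in a limited form. The Data analysis section lets observed skewness, by an unstated criterion, choose between two different hypotheses for the primary pain scores. Only one of them is the difference in means in mm on which the trial is sized.

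Rejection of equal means rises to about 10% or 20% in the two unequal-spread cases shown, against about 5% for Welch t. These figures rest on assumed beta-shaped scores, an assumed Mann–Whitney test and an assumed skewness test at 0.05. They show what can happen and do not predict this trial's error rate.

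This should be corrected because it is real and cheap to correct. It does not invalidate the design. If the full analysis plan already names one mean-based analysis for the VAS scores, the two documents only need to be brought into line.

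**What to change.** For neck and arm pain on the VAS, replace the skewness rule with one analysis named in advance:

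- **Primary analysis:** the difference in mean VAS between arms, adjusted for the baseline VAS that is already collected, by ANCOVA or a mixed model with robust standard errors. Use it whatever the distribution looks like, and in the same form for both scores and all visits.
- **Missing data:** fit this model in each imputed data set and pool the estimate and standard error by Rubin's rules.
- **Sensitivity analysis:** a rank-based or bootstrap comparison, named as such. If it is rank-based, state the estimate to be pooled.
- **Secondary outcomes:** rank or ordinal methods may stay for ordinal scales, assigned by type of scale and not by observed skewness.

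The cost is wording only. The sample size stays at 56 per group before drop-out. The price is some power if the data are strongly skewed: about 80% against 91% for a rank test in the assumed case with means 25 and 40. The mean comparison still keeps the 80% that the plan states, for the quantity that it states. Baseline adjustment is a separate improvement; removing the skewness rule does not depend on it.
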